Case-cohort studies with time-to-event outcomes require non-standard statistical analyses but those with binary outcomes do not [10]. Thus statistical analysis of both cohort and case-cohort designs will be performed using logistic regression [11]. In order to avoid over-fitting of models, multivariate analyses will use a cross validation approach. A model will be fitted on 90% of the given study group and then the probability of the outcome calculated for each member of the remaining 10%. This process will be repeated until "out of sample" estimated probabilities are obtained for all participants in the given analysis. The screening performance of the models will be assessed using this predicted probability in two ways. First, the area under the receiver operating characteristic (ROC) curve will be estimated, with 95% confidence intervals as a summary of its discrimination. Different models will be compared using the method of DeLong et al [12]. Second, the screening performance of models will be assessed by analysis using percentiles of predicted probability, where women in the top 5%, 10% or 20% of predicted probability are regarded as screen positive. The screening performance of each of the thresholds will then be summarized in terms of sensitivity, specificity, positive and negative predictive values and likelihood ratios.

Finally, we also plan to conduct nested case-control studies within the cohort. This approach will be used where very expensive or labour intensive methodologies are planned, such as proteomic analysis of serum or gene expression array analysis of placental RNA, and will involve sampling of cases as well as controls. These methods are generally utilized in studies trying to understand the biology of adverse pregnancy outcome or to identify novel biomarkers. Nevertheless, the possibility of confounding is still present with these approaches. Multivariate analysis is impractical using these methods, given that small numbers are employed. Our approach is to perform a nested case-control design with one to one matching of cases and controls on key maternal characteristics to address the potential for confounding. Subsequent analyses will, therefore, utilise paired statistical methods.

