A distinctive feature of the present study is that relatively basic information is retrieved about the mother. This is in contrast to the SWS where a 90 minute interview was conducted prior to the pregnancy and food frequency questionnaires and diaries were administered both in early and late pregnancy. It is also in contrast to the SCOPE study. This involves a 60–90 minute interview at 15 weeks and a 45 minute interview at 20 weeks. As other studies are addressing the factors that can only be ascertained through questionnaires, there is less impetus to have a further study addressing the same issues. Moreover, detailed questionnaires addressing environmental, dietary and social history are time consuming to administer. This reduces the number of women who can be recruited for a given number of personnel hours. It also may serve as a relative obstacle to recruitment if women feel inhibited about a prolonged and detailed interview. In order to optimise recruitment, the present study was designed to make involvement attractive to potential participants. The total time involved through participation in this study is less than two hours across all four visits. Moreover, more than half of that time is spent having ultrasound scans performed and women generally feel very positive about ultrasonography in pregnancy [23]. We interpret the greater than 50% recruitment rate and the very low drop out rate as confirming the attractiveness and acceptability of this study design. The attractiveness of participation is important as it may tend to encourage women from a wider range of social and educational backgrounds. A design which systematically recruits very highly motivated and educated women will result in reduced rates of adverse events and a highly selected population may also adversely affect a study's external validity. Finally, our study has at its core the aim of assessing markers of placentation in the prediction of pregnancy outcome. The study design reflects our belief that combined ultrasonic and biochemical assessment of the placenta is likely to be a better predictor of adverse outcome than maternal dietary or other history.

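### For nested models, the DeLong comparison on pooled cross-validated probabilities is not a calibrated test of added value; modest gains and gains for rare outcomes will often be missed

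*Protocol article*

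**What the plan says.** The relevant text is in the Protocol article, section Analytic approach. On the model class: "statistical analysis of both cohort and case-cohort designs will be performed using logistic regression". On over-fitting: "A model will be fitted on 90% of the given study group". The remaining tenth is then scored, and the cycle continues until each participant has a prediction from a model that did not use her data. From these predictions "the area under the receiver operating characteristic (ROC) curve will be estimated, with 95% confidence intervals". The rule for choosing between models follows: "Different models will be compared using the method of DeLong et al". It carries no limit to non-nested models, and no other between-model test is given.

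A second strand does not involve DeLong: "women in the top 5%, 10% or 20% of predicted probability are regarded as screen positive", summarised by sensitivity, specificity, predictive values and likelihood ratios. The Power calculations section treats sensitivity at a fixed screen-positive rate as a key quantity. No effect size, significance level or power is stated for the model comparison.

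**The concern.** DeLong's variance treats the two sets of scores as fixed. Here they come from repeated logistic fits. When one model contains the other and the extra term carries no information, estimating its coefficient slightly worsens out-of-sample discrimination. The AUC difference is then centred below zero instead of at zero, and its standard error is understated. Near this null the ratio of difference to standard error is also not close to normal.

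The study exists to learn whether scans and biomarkers improve prediction. If the only named comparison has the wrong size and leans against the larger model, a useless marker may be reported as significantly harmful and a modest real gain as absent.

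Pooling adds a separate problem when events are few. A fold that happens to hold more cases is scored by a model fitted to fewer cases, hence with a lower intercept, and this depresses the pooled AUC.

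**Working it through.** **The plan's own figures.** Exact binomial 95% intervals for 80% sensitivity are 73.8–85.3% (200 cases), 70.8–87.3% (100), 66.3–90.0% (50) and 56.3–94.3% (20). All match Power calculations. Expected cases: 0.03 × 2000 = 60, 0.03 × 4000 = 120 and 0.005 × 4000 = 20, which also match. There is no stated error rate for the DeLong comparison to reproduce.

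**Inputs from the article.** Cohort of 4000; about 120 small-for-gestational-age infants below the 3rd percentile, about 80 pre-eclampsia cases, 150–200 preterm births and about 20 stillbirths (Discussion); logistic models and 90%/10% cross-validation (Analytic approach).

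**Assumptions not in the article.** Ten folds; two-sided 0.05; normal covariates; a base model of 4 or 6 covariates with cross-validated AUC about 0.68–0.69 (0.64 with 20 cases); one independent added marker with OR per SD from 1.0 to 2.5; a 10% sub-cohort in one case-cohort setting.

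**Statistics.** DeLong: z = (AUC₁ − AUC₀)/SE, with the paired SE, on pooled out-of-sample scores. Reference: likelihood-ratio statistic 2(ℓ₁ − ℓ₀) on χ² with 1 df, full data. There were 600 replicates per setting, so the Monte Carlo SE at 23% is √(0.23 × 0.77/600) = 1.7 points.

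**Useless marker (OR 1.0).**

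| Cases | Mean AUC difference | DeLong rejects (two-sided) | Favours marker |
|---|---|---|---|
| 20 | −0.0073 | 17.7% | 0.7% |
| 81 | −0.0023 | 23.5% | 0.0% |
| 122 | −0.0015 | 23% | 0.3% |
| 122, 10% sub-cohort | −0.0019 | 20.0% | 0.0% |
| 183 | −0.0010 | 22.2% | 0.2% |

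The nominal figures are 5% in total and 2.5% in favour. The likelihood-ratio test rejected in 3.5–6.3%. Other runs with base AUC about 0.70 and 120 cases gave 20–23% worse and 0–0.3% better.

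The shift and the understated SE explain only part of this. With 81 cases the mean difference is −0.0023, its observed SD 0.0045 and the mean DeLong SE 0.0041. A normal approximation gives Φ((−1.96 × 0.0041 + 0.0023)/0.0045) = Φ(−1.27), about 10%, against 23.5% observed. The rest reflects the non-normal shape.

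**Real marker: percentage of runs in which it is detected.**

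| OR per SD | 1.22 | 1.35 | 1.50 | 1.73 | 2.00 | 2.50 |
|---|---|---|---|---|---|---|
| DeLong, 20 cases | 3 | 5 | 10 | 22 | 37 | 62 |
| DeLong, 81 | 2 | 12 | 31 | 68 | 92 | 99.7 |
| DeLong, 122 | 3 | 19 | 49 | 88 | 99.5 | 100 |
| DeLong, 122, 10% sub-cohort | 2 | 12 | 36 | 75 | 96 | 100 |
| DeLong, 183 | 8 | 34 | 72 | 99 | 100 | 100 |
| Likelihood ratio, 20 | 14 | 28 | 43 | 68 | 86 | 97 |
| Likelihood ratio, 122 | 55 | 89 | 99 | 100 | 100 | 100 |
| DeLong, true coefficients, about 120 | 13 | 27 | 46 | 76 | 92 | not run |

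The last row (400 replicates) involves no fitting and shows what comparing AUCs costs by itself. Taking all runs with 80–120 cases together, detection was 7–19% at OR 1.35 and 58–88% at OR 1.73.

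**Pooling with 20 cases.** With a single predictor of true AUC 0.700, the pooled AUC averaged 0.665–0.673 and the 95% interval covered in about 87–91% of runs. Stratifying folds on outcome restored these to 0.690 and 95%. It did not repair the test: with a useless marker it still called the larger model worse in 22–26% of runs.

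**The case against.** The article never says that the compared models are nested. The Discussion sentence that comes closest, holding that "combined ultrasonic and biochemical assessment of the placenta is likely to be a better predictor of adverse outcome", goes on to contrast placental assessment with maternal history; taken literally, that pair is not nested. This stands: nesting is an inference. It is a natural one, because the study collects maternal data on everyone and sets out to evaluate scans and biomarkers in multivariate models. The rule as worded covers such comparisons.

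A reader might go further and infer that real added value will usually be missed, or that the study would answer no by construction. The documents do not support this. No target effect is stated, and with 80 or more cases strong markers are usually found.

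The gap to the likelihood-ratio test is also partly a difference of question. That test asks whether a coefficient is non-zero; the plan asks about screening performance. At OR 1.35 and 120 cases, DeLong with true coefficients reaches only 27%, so cross-validation is not the sole cause of low power. Such a marker is also small for screening: with two normal distributions, base AUC 0.700 and 3% incidence, AUC rises to 0.714 and sensitivity at a 10% screen-positive rate goes from 28.3% to 30.2%.

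Finally, the percentile-based analysis does not rely on DeLong, and the article already meets the scarcity of stillbirth with open-ended recruitment and proxy outcomes. Fold details are something an article may leave to the full plan; they matter here only as part of the remedy. None of this restores the size of the test, which was wrong in every setting examined and depends on no assumed marker effect.

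**Conclusion.** The point holds in limited form. Applied to nested logistic models, the stated comparison is miscalibrated: about four times the nominal two-sided error, nearly all of it against the larger model, and almost no chance of favouring a useless marker. Modest gains with 80–120 cases, and most gains with about 20 cases, will often go undetected; part of that loss is inherent in comparing AUCs. Strong markers with 80 or more cases are usually found, so a general claim of missed value would overreach. The downward bias in AUC from pooling was shown for about 20 cases.

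The size result rests on ten folds, a two-sided 5% level and a base AUC near 0.70, and was stable from 20 to 183 cases and in the case-cohort setting. The detection rates depend in addition on the assumed marker strength. The percentile-based sensitivity results are not touched by the choice of test.

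**What to change.** - For nested models, test added value by the likelihood-ratio test of the added terms in the logistic model.
- Report the change in cross-validated AUC as an estimate of screening gain, with a confidence interval from resampling that repeats the whole fit and cross-validation each time.
- For rare outcomes, stratify the folds on outcome. This addresses the AUC bias only, so it does not replace the change of test.
- Keep DeLong for non-nested scores fixed in advance.
- State that a significant likelihood-ratio test shows association, and is to be read with the AUC change and with sensitivity at the 5%, 10% and 20% thresholds before a marker is called useful.

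The cost is plan wording and computing time. Recruitment, sampling and data collection are unaffected.

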### Power calculations

Clearly power calculations cannot be performed prospectively for all potential analyses in the study. Moreover, we aim to study a series of adverse outcomes which have different incidence rates. A key measure we aim to determine is the sensitivity of different models for a given screen positive rate. The precision of any estimate of sensitivity can be quantified by the 95% confidence intervals. If we take the example of a model with 80% sensitivity, the 95% CI will be 74–85% for 200 cases, 71–87% for 100 cases, 66–90% for 50 cases and 56–94% for 20 cases. Taking the example of a condition with 3% incidence (e.g., delivery of an infant with birth weight less than the 3^rd ^percentile), we would obtain 60 cases with a cohort of 2000 women and 120 cases with 4000 women. Hence, the study is likely to provide reasonably precise estimates of sensitivity for conditions with a 3% incidence. The incidence of preterm birth and pre-eclampsia are both likely to be slightly higher [13,14]. However, the incidence of some other complications, such as stillbirth, typically 0.5% in nullipara, will be lower [15]. Hence, we have an open ended plan for recruitment, as the study will progressively achieve power for the less common adverse outcomes with greater cohort size.

### Initial experience with study

This study commenced at the Rosie Hospital, Cambridge UK on the 14^th ^of January 2008. Over the first six months, a total of 588 eligible women were approached and 340 (57.8%) agreed to participate in the study and provided written consent. Over this period 4 (1.2%) women have withdrawn, two of whom have relocated. No woman has withdrawn due to any problems with the conduct of the study and no significant negative feedback has been given, formally or informally.

## Discussion

We describe a simple design for a prospective cohort study of unselected primiparous women. We will compare this study with two other large scale prospective cohort studies in pregnancy, namely, the Southampton Women's Survey [16] and SCOPE [17]. The Southampton Women's Survey (SWS), funded by the MRC in the UK, was a prospective cohort study which recruited women in their reproductive years and then aimed to study these women during their pregnancy. A total of 12,500 women were approached and approximately 3000 liveborn infants are to be studied through childhood. SCOPE is a multicentre prospective cohort study recruiting primiparous women at around 15 weeks gestational age. It commenced in Auckland, New Zealand, but now also has centres in Australia, the UK and Ireland and is still actively recruiting. Each study will have its strengths and drawbacks. We will briefly discuss the rationale for the approach we have taken.

In our study, we have limited recruitment to primiparous women. There were essentially four reasons for doing so. First, primiparity is associated with increased risks of a number of adverse outcomes of pregnancy, including preterm birth, pre-eclampsia, stillbirth and intrapartum caesarean section [18-20]. By focusing on primiparous women, there will be a greater proportion of the cohort who experience adverse events. Second, one of the best predictors of the outcome of pregnancy is the outcome of a woman's previous pregnancy. This information is clearly not available for primipara, hence, there is a particular need for tests to predict risk in this population. Third, any model derived from women of mixed parity would have to incorporate previous pregnancy outcome for those who were multiparous. In a cohort of mixed parity, this information will be variably present and hence complicate the process of modelling. Finally, we plan to run this study for at least 4 years. It is likely that a sub-set of women will attend the hospital for consecutive pregnancies. This would mean that, within the cohort of pregnancies, some would be to the same women. Non-independence of observations is a further complicating factor for statistical analysis.

One feature of the present study is that we aim to recruit women early in pregnancy. We have done this as there is considerable evidence that complications in late pregnancy may be determined to a large extent in the first trimester (see Smith 2004 [21] for review). Women in the SWS cohort were recruited pre-pregnancy. However, this was a major undertaking and the ratio of women approached to women who were followed through to pregnancy was greater than 4:1. While there are clearly real strengths in a study design where pre-pregnancy data are available, this involves the expense of retrieving information from large numbers of women who do not have a pregnancy in the timescale of the study. Understanding the relationship between a mother's diet prior to pregnancy and the subsequent health of her child was a key issue in the SWS but is not a focus of the present study, hence the different approach.

A important feature of the present study is that we perform serial scans and phlebotomy through all three trimesters of pregnancy. The SWS study performed scans at 19 and 34 weeks and the SCOPE study at 20 and 24 weeks. The rationale for first trimester assessment is developed above. The basis for scans and phlebotomy at 28 and 36 weeks, in addition to the early sampling, is previous analyses of other datasets. We have previously reported the association between circulating concentrations of alpha fetoprotein and human chorionic gonadotrophin in maternal blood at 15–20 weeks gestation and the risk of stillbirth [15]. Both measures were much better predictors of stillbirths at extreme preterm gestation than losses in later pregnancy. Similarly, high resistance patterns of uterine artery Doppler flow velocimetry at 23 weeks gestation are strongly predictive of stillbirth at extreme preterm gestations, but weakly associated with later losses [22]. The primary intervention to prevent stillbirth is elective delivery and this carries serious risks to the mother and infant if performed at extreme preterm gestations. This provides a rationale for improving methods of detecting babies at risk of stillbirth at later gestational ages (see review [2]). Hence, we have included ultrasonic and biochemical tests at later gestations.

A distinctive feature of the present study is that relatively basic information is retrieved about the mother. This is in contrast to the SWS where a 90 minute interview was conducted prior to the pregnancy and food frequency questionnaires and diaries were administered both in early and late pregnancy. It is also in contrast to the SCOPE study. This involves a 60–90 minute interview at 15 weeks and a 45 minute interview at 20 weeks. As other studies are addressing the factors that can only be ascertained through questionnaires, there is less impetus to have a further study addressing the same issues. Moreover, detailed questionnaires addressing environmental, dietary and social history are time consuming to administer. This reduces the number of women who can be recruited for a given number of personnel hours. It also may serve as a relative obstacle to recruitment if women feel inhibited about a prolonged and detailed interview. In order to optimise recruitment, the present study was designed to make involvement attractive to potential participants. The total time involved through participation in this study is less than two hours across all four visits. Moreover, more than half of that time is spent having ultrasound scans performed and women generally feel very positive about ultrasonography in pregnancy [23]. We interpret the greater than 50% recruitment rate and the very low drop out rate as confirming the attractiveness and acceptability of this study design. The attractiveness of participation is important as it may tend to encourage women from a wider range of social and educational backgrounds. A design which systematically recruits very highly motivated and educated women will result in reduced rates of adverse events and a highly selected population may also adversely affect a study's external validity. Finally, our study has at its core the aim of assessing markers of placentation in the prediction of pregnancy outcome. The study design reflects our belief that combined ultrasonic and biochemical assessment of the placenta is likely to be a better predictor of adverse outcome than maternal dietary or other history.

When designing the present study, a key question was whether information obtained through a research scan should be used for ad hoc screening of research participants. With the very few exceptions we allowed, the position in this study was that the research scan data should not be so employed. However, women have all ultrasonic investigations that are normally conducted and have any additional scans requested by the attending obstetrician, i.e. participating in this study does not alter in any way the routine or targeted scanning requested by clinical staff caring for those recruited. The basis for concealing the research scan information was recommendations from NICE in the UK. Their guideline on antenatal care, which is intended to inform all NHS activity in the UK, explicitly states that routine Doppler and growth studies should not be performed on unselected women [3]. The basis for their position is the result of meta-analyses of randomised controlled trials of these methods which failed to show any benefit [6,7]. We flagged this issue in our application for ethical approval and the study received approval. Other studies have, however, taken different views. The SWS study revealed the results of a growth scan at 34 weeks. The SCOPE study reveals the following information: cervical length <15 mm at 20 weeks, absent or reversed end diastolic velocity on umbilical artery Doppler at 24 weeks, and abdominal circumference <10^th ^percentile at 24 weeks.

The initial target recruitment for the present study is 4000 women. We estimate that this would yield approximately 120 cases of small for gestational age infants (using the strict definition of <3^rd ^percentile), 150–200 preterm births, and about 80 cases of significant pre-eclampsia (the number of cases of pre-eclampsia will depend on the stringency of the diagnosis). These should be adequate for most analyses planned. However, antepartum stillbirth unrelated to congenital abnormality affects about 0.5% of unselected primigravid women who attend for prenatal screening [15]. Hence, we would anticipate only approximately 20 such events. This is the basis for planning open-ended recruitment. However, samples from small numbers of women experiencing rare events will still be used to identify novel biomarkers using techniques such as proteomics and there may be potential to validate candidate markers in other cohorts. We will also use non-lethal complications of pregnancy, such as intra-uterine growth restriction, abruption and severe pre-eclampsia, as proxies for stillbirth. This is consistent with the view that similar processes operate in the lethal and non-lethal manifestations of these conditions [24].

The study is designed both to provide samples to evaluate blood tests as predictors of adverse pregnancy outcome and to provide very well phenotyped pregnancy outcome for basic science studies. In the former case, we will use multivariate modelling to address potential confounding. In the latter case, samples will be provided for basic science studies as matched cases and controls. Many translational research studies which employ an observational design essentially ignore the possibility of confounding. However, women who experience pregnancy complications exhibit multiple differences when compared to the healthy population. Moreover, medical interventions will tend to be used selectively. Taking an example of Western blot analysis of placental expression of a protein comparing women with and without pre-eclampsia, the cases and controls are likely to differ in relation to age, parity, obesity and smoking status [13,25]. Moreover, women with pre-eclampsia are more likely to be delivered preterm and more likely to be delivered by planned caesarean section. Many studies applying basic science methods to the study of human clinical material fail to account adequately for these systematic differences and many such analyses are conducted in a way that would be unacceptable in clinical epidemiological research. We will address this using a nested case-control design with one to one matching on key maternal characteristics. This approach reflects a key aim of this study i.e. to combine excellence in science with excellence in clinical research design and analysis.

In summary, we present a simple pragmatic design for a prospective cohort study of unselected primigravid women. This involves quite intensive scanning, phlebotomy and collection of other samples, but appears to be acceptable to the majority of such women in our initial experience.

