### Delivery

Pregnant women receiving antenatal care in the UK National Health Service generally carry hand held notes. Women participating in the study have their hand held notes contained in a plastic folder with the study logo to flag their participation. Moreover, a sticker is placed in the delivery unit section of the notes to flag the need for placental collection and a sheet with instructions is included in the notes. This sheet includes the number for a phone held by the on-call technician. If a woman delivers at a time when a technician is present in the hospital, the placenta is passed to the technician as soon after delivery as practicable. The placenta is sampled as described in the schematic shown in Figure 1. Details of the collection protocol for the samples to be used for histological, DNA, RNA and protein analyses are given in Table 2. If the woman delivers at a time when there is no technician present, the placenta is placed in a dedicated fridge and the samples processed the following morning. The details again are described in Table 2.

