**Basic level collection**	
Placenta is stored in a fridge and sampled within 24 hours of delivery.	

1. Placenta	Four 'grape size' samples are obtained and washed as described above. From each 'grape' sample, the following are obtained:
	i. DNA & protein: Four 50 mg pieces, frozen at -80°C.
	ii. Histology: A "pea-sized" sample is fixed in 3 ml of formalin as above.
2. Placental membranes	A 2 × 2 cm portion of the membranes is obtained and fixed in formalin as above.
3. Umbilical cord	The following samples are obtained
	i. DNA & protein: Two 100 mg pieces of cord, frozen at -80°C.
	ii. Histology: One 5 mm transverse section of cord is fixed in formalin as above.

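### For placenta, membrane and cord studies, matching on maternal characteristics does not control the delivery differences that the protocol itself names, and nothing stated keeps pairs within one collection level

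*Protocol article*

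**What the plan says.** The Discussion takes a Western blot of placental protein in pre-eclampsia as its example of confounding in laboratory work. It names maternal differences first: "the cases and controls are likely to differ in relation to age, parity, obesity and smoking status". It then names delivery differences: "women with pre-eclampsia are more likely to be delivered preterm and more likely to be delivered by planned caesarean section". It criticises other studies for not accounting for such differences and gives its own remedy: "We will address this using a nested case-control design with one to one matching on key maternal characteristics".

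The Analytic approach section has the same remedy, "one to one matching of cases and controls on key maternal characteristics to address the potential for confounding". It closes off the alternative, "Multivariate analysis is impractical using these methods, given that small numbers are employed", and fixes the analysis: "Subsequent analyses will, therefore, utilise paired statistical methods".

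On handling, the Delivery section says: "If the woman delivers at a time when there is no technician present, the placenta is placed in a dedicated fridge". Table 2 sets out two levels. The immediate level is completed within 10 minutes, and its placental DNA and protein pieces are frozen in liquid nitrogen. For the basic level, "Placenta is stored in a fridge and sampled within 24 hours of delivery", and the corresponding pieces go to -80°C with no liquid nitrogen step. RNA and cord blood are listed only at the immediate level. Placental protein, DNA and histology, membranes and cord are listed at both.

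**The concern.** The Discussion sets a standard, that systematic differences between cases and controls must be accounted for, and offers a remedy that reaches only some of the differences it lists. Gestational age at delivery and mode of delivery describe the birth, not the mother. Matching on maternal characteristics therefore leaves them free to differ within a pair, and no adjustment is planned to pick them up.

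What is at stake is the reading of a placental protein, histology or expression difference. It could reflect gestation, labour or time in a fridge instead of the disease. A paired test removes only what the two members of a pair share, so a factor that differs within pairs stays in the paired difference. More pairs do not help: the bias stays the same while the standard error shrinks, so a spurious finding becomes more likely.

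**Working it through.** **No plan figure to reproduce.** The article gives no number of pairs, SD, effect size or power for the nested studies. Its precision figures, under Power calculations, concern sensitivity and do not bear on this point. The finding rests on setting the sections side by side. The arithmetic only illustrates it.

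**Step 1. Stated differences against the stated rule.**

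| Difference | Where it appears | Reached by maternal matching? |
|---|---|---|
| Age, obesity, smoking | Discussion | Yes, if on the matching list |
| Parity | Discussion | Largely fixed already by recruiting primiparous women |
| Preterm delivery | Discussion | No |
| Planned caesarean section | Discussion | No |
| Collection level | Not named as a confounder; inferred from Delivery and Table 2 | No |

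No section names gestational age at delivery, mode of delivery or collection level as a factor for matching, restriction or adjustment. The Discussion reserves multivariate modelling for the evaluation of blood tests and gives basic-science studies matched samples instead.

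**Step 2. Which assays are affected.**
- Serum and plasma from the scheduled antenatal visits: mode of delivery and placental handling cannot act on them, so they are outside the point.
- Placental RNA: listed only at the immediate level, so it cannot mix levels. Gestation and mode of delivery still apply.
- Placental protein, DNA and histology: both gaps apply. Membranes and cord: both apply, but the levels differ there in delay and not in the stated freezing or fixing step.

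**Step 3. Illustration for collection level.** All inputs are assumed; none comes from the article. Take a protein with no true association and SD 1, independent members within a pair, immediate collection in 60% of cases and 30% of controls, a storage effect s of 0.5 or 1.0 SD, and 50 pairs.
- Spurious mean difference = (0.60 − 0.30) × s = 0.15 or 0.30 SD.
- Standard error of the mean paired difference = √2/√50 = 0.20.
- Standardised shift z = 0.15/0.20 = 0.75, or 0.30/0.20 = 1.5.
- Two-sided rejection = Φ(−1.96 + z) + Φ(−1.96 − z) = about 12% or 32%, against a nominal 5%.

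If the SD of 1 is meant within a collection level, the mixture adds variance:
- Variance of a paired difference = 2 + s²(0.6×0.4 + 0.3×0.7) = 2 + 0.45s², that is 2.11 or 2.45.
- Standard error = √(2.11/50) = 0.206, or √(2.45/50) = 0.221.
- z = 0.73 or 1.36, and rejection = about 11% or 27%.

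**Step 4. Wider range.** Use the same model with the added variance. The factor (a delivery factor or collection level) is present in 30% of controls and in D = 10 to 40 percentage points more of the cases, and again shifts the marker by 0.5 to 1.0 SD. The bias is D × s, from 0.05 to 0.40 SD.

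| Pairs | Lowest (D = 10, s = 0.5) | Highest (D = 40, s = 1.0) |
|---|---|---|
| 20 | 5.3% | 21% |
| 40 | 5.5% | 37% |
| 80 | 6.1% | 63% |

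The Discussion expects about 80 cases of significant pre-eclampsia from 4000 women, so 80 pairs is about the most that this outcome could supply at the initial target.

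**The case against.** The strongest reply is that this is a journal article. It does not itemise the key maternal characteristics, and a fuller document could list the matching factors for each laboratory study. That answers a complaint that sample handling is not listed. It does not fully answer the delivery factors: the article names them as differences and says that matching of a stated kind addresses them, and on an ordinary reading that kind does not include them.

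The second reply concerns gestational age, and it stands. Preterm delivery is partly a consequence of pre-eclampsia, so matching on it changes the question. Preterm controls are not healthy controls either, since the study counts preterm birth among its own adverse outcomes. Exact matching on gestation should not be demanded.

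Third, the handling argument is partly inference, and this also stands. A reader might infer that planned caesareans fall in technician hours, so that cases are collected immediately more often. The article gives no technician hours, mentions an on-call technician reached by phone, and does not say that levels differ by case status or that cross-level pairs will be used.

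A reader might also infer that every nested study is affected. Serum taken at antenatal visits is not, and RNA cannot mix levels. Finally, these studies serve biology and biomarker discovery. The primary aim, screening performance, uses cohort and case-cohort models and is untouched.

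**Conclusion.** The point holds for nested case-control studies of samples taken at delivery. As written, one-to-one matching on maternal characteristics with paired analysis leaves uncontrolled the preterm and planned-caesarean differences that the Discussion names, and no other section closes the gap. This part rests on the text alone, with the single assumption that maternal characteristics carries its ordinary meaning.

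The collection-level part is weaker. Two handling routes and the absence of a stated bar on cross-level pairs are in the document; an imbalance between cases and controls is plausible but not stated. Collection level should not be described as a confounder that the protocol names.

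The 12% to 32% (or 11% to 27% with the mixture variance) shows how the mechanism works on assumed inputs. It is not an estimate of this study's error rate; Step 4 shows that the result can lie anywhere from barely above 5% to above 60%. The point should be corrected before pairs are drawn, but it does not threaten the main screening analyses.

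**What to change.** For assays on placenta, membranes and cord, replace the claim that maternal matching deals with these differences by a selection rule:
- Pair only within the same collection level, never an immediate-level with a basic-level sample.
- Match on mode of delivery (pre-labour caesarean or labour) in addition to the maternal characteristics.
- For gestational age at delivery, match where suitable controls exist. Where they do not, restrict the comparison or run a sensitivity analysis, and report the remaining difference as residual confounding.

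Pairs are drawn later from stored tissue, so the design and the collection procedures stay as they are. Mode of delivery and gestation should be available through the link to the Delivery Unit record described under Ascertainment of outcome. The article does not say that collection level is recorded with each placental sample, so that field must be confirmed or added.

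The costs are fewer eligible controls per case and some unmatched cases, mainly preterm ones. With about 80 pre-eclampsia cases expected, the number of pairs that survive the rule should be counted before an assay is commissioned.
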